#### 3.19.2. Sensor Data Analysis

See Table 2 for a summary description of the data to be collected and the proposed derived parameters for further analysis.

### 3.20. Feasibility

Feasibility parameters in preparation for a main trial will be assessed and practicalities about the study delivery evaluated. These include completion and withdrawal rates, completion of questionnaires at baseline, post-intervention and follow up but also other outcomes such as management resources (i.e., monitor time for managing the trial and data, resources required for assessment and delivery of the intervention and time for data entry and data analysis. Scientific outcomes will also be captured as indicators of acceptability of the measures used.

## 4. Trial Status and Ethics Approval

Awaiting ethics approval. Not yet recruiting.

## 5. Patents

No patents applied for.

## Figures and Tables

**Figure 1 healthcare-08-00011-f001:**
[figure not shown]
A computer model of the KiTE seat to be used for the study, showing the dynamic foot, thigh and back supports. The seat is mounted on a standard mobile base as used in classrooms and domestic environments.

**Figure 2 healthcare-08-00011-f002:**
[figure not shown]

[figure not shown]
(**a**) Flow chart of baseline measurements and assessments. This chart should be read in conjunction with Table 1. (**b**) Flow chart of intervention period measurements and assessments. This chart follows Figure 2a and should be read in conjunction with Table 1.

**Table 1 healthcare-08-00011-t001:** Study assessments and participant journey timeline. The baseline and intervention processes are described with flow charts in Figure 2a,b.

	Enrolment	Assessments							Transition Visits (Configure Seat)		Post-Allocation								Review				Close Out
		Baseline									Intervention (8 Weeks)								Post		Follow Up		
		(Duration Randomised between 2 and 7 Weeks)																					
TIMEPOINT	e1	b1	b2	b3	b4	b5	b6	b7	c1	c2	t1	t2	t3	t4	t5	t6	t7	t8	p1	p2	f1	f2	co1
**ENROLMENT**																							
Participant Identification	X																						
Eligibility Screen	X																						
Participant Recruitment (Including Consent)	X																						
Randomisation (From b1–b2 to b1–b7)	X																						
**INTERVENTION**																							
Dynamic seat provision																							
**ASSESSMENTS**																							
GMFCS	X																						
mini-MACS/MACS	X																						
Demographics	X																						
BFMDRS (Dystonia)	X																		X				
**TIMEPOINT**	e1	b1	b2	b3	b4	b5	b6	b7	c1	c2	t1	t2	t3	t4	t5	t6	t7	t8	p1	p2	f1	f2	cc1
PQRS (Task Performance)		xxx	xxx	xxx	xxx	xxx	xxx	xxx			xxx	xxx	xxx	xxx	xxx	xxx	xxx	xxx	X				
COPM (Goal Attainment)		X																		X		X	
Seat Occupancy (Sensor)		X	X	X	X	X	X	X			X	X	X	X	X	X	X	X		X		X	
RAACS (Communication)		X																		X		X	
Sleep Quality (Sensor)		X	X	X	X	X	X	X			X	X	X	X	X	X	X	X					
QoL (PedsQL)		X																		X		X	

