### 3.10. Primary Outcomes

There will be three primary outcome measures. Two complementary co-primary objective outcome measures will be employed: the first one will be a subjective rating scale to explore parents/carers perceived performance and satisfaction on a number of self-selected goals using the Canadian Occupational Performance Measure (COPM) [17]. Secondly, the Performance Quality Rating Scale (PQRS) [18] will be used to measure the individual goals selected for the intervention and will be blind-rated. Further, seating tolerance will be objectively measured using sensors attached to the chair that will capture the duration and frequency of its use throughout the baseline and intervention and follow-up periods.

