### 3.12. Baseline Assessments for Treatment Planning

One assessment will be used to establish goals for intervention: COPM [17]. This assessment will also be used as outcome measure

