### 3.14. Description of Standard Care

Participants will be randomised to length of baseline and the same measurements will be acquired during this period when the child will be using their usual static seating system (chair). As the provision of static seating tends to differ across the country, we will capture this data as part of the feasibility parameters captured. We will record other type of standard care that participants receive including occupational therapy, physiotherapy and any other early intervention.

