### 3.15. The Seat Intervention

The specifically designed dynamic seating system will be set-up by a qualified occupational therapist/physiotherapist and an engineer from the study team. The intervention (dynamic chair provision) will consist of a trial of 8 weeks. Figure 1 shows the seat model that will be trialled. A researcher will visit the child and family once per week to measure goals set up by the family. This, in itself, could be considered an intervention as the family might not have set clear goals if they were not involved in the trial. These visits will be video recorded for subsequent scoring and review.

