#### Outcome Evaluation

Primary and secondary outcome measures across activity and participation domains will be completed at baseline (b1–b7, with baseline length randomly allocated), during intervention (for repeated measures such as PQRS, sensor based data and accelerometers) (t1–t8), post intervention (p1, p2) and follow up (f1, f2) and include the COPM, PQRS, seat occupancy, RAACS, Peds-QL, time to target, path complexity, reaching performance and sleep quality.

Response will be tracked using multiple video recordings during sessions of goals identified for intervention as well as with sensor data and data from accelerometer. The Performance Quality Rating Scale (PQRS) will be used for goals, and sensor data for seat occupancy, and frequency and intensity of movement in bed as an indicator of sleep quality. Data points will be collected at baseline (b1–b7), during intervention (t1–t8); post-intervention (p1) and 2 month follow up (f2). There will be a minimum of 3 video-recorded baseline assessments of each goal before intervention and minimum of 3 trials post intervention and at 2 months review. Further, outcome evaluation measures outlined above will be completed at t1 and t2. The PQRS will be rated by an independent observer using video recordings. The videos from baseline, post-test and follow up will be presented in a randomized non-chronological order. A third party will complete assessments at baseline and post treatment. PQRS will be scored blinded by another occupational therapist using video recordings randomly presented.

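### In Table 1 COPM, a primary outcome, is rated only once before the seat, so any COPM change during the randomised baseline is counted in the change attributed to the seat

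*Protocol article*

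**What the plan says.** Section 3.10 names three primary outcomes. One is used to "explore parents/carers perceived performance and satisfaction on a number of self-selected goals using the Canadian Occupational Performance Measure (COPM"). Section 3.12 gives the same instrument a second job: "One assessment will be used to establish goals for intervention: COPM", followed by "This assessment will also be used as outcome measure".

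The places that describe when COPM is rated do not agree:

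- **Table 1.** The row "COPM (Goal Attainment") has marks at b1, p2 and f2. The row "PQRS (Task Performance") has three marks in every baseline week and every treatment week, then one at p1.
- **Section 3.17, Outcome Evaluation.** "Primary and secondary outcome measures across activity and participation domains will be completed at baseline (b1–b7, with baseline length randomly allocated"), and COPM is in the list that ends that sentence. The section later adds ratings of the outcome measures at t1 and t2, which the COPM row of Table 1 does not show.
- **Section 3.14.** During baseline "the same measurements will be acquired during this period when the child will be using their usual static seating system (chair").

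Section 3.15, on the weekly visits that measure the family's goals, says: "This, in itself, could be considered an intervention as the family might not have set clear goals". Section 3.19 plans means with 95% confidence intervals for overall change in all measures. Section 3.19.1 uses raw scores before and after the intervention, in all outcomes, to describe its impact.

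**The concern.** Section 3.1 presents each child as their own control, with at least 5 baseline assessments, and section 3.5 recommends at least 3. Section 2.3 makes within-period variance a primary aim. Under Table 1, COPM has one baseline value, at the first baseline visit, and so meets none of these.

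For PQRS and seat occupancy, repeated baseline values show whether a child was already changing in the usual seat. For COPM nothing does. The b1-to-p2 change spans the whole randomised baseline, the transition visits and the seat period, and the plan reads it as the effect of the intervention. Any change that comes from setting goals, being visited or the passing of time before the seat arrives is included. The length of that exposure differs between children because it is randomised. COPM is also reported by unblinded parents or carers, so blind video rating does not protect it. The study is meant to supply effect sizes and variances for a later trial, and a COPM estimate mixed in this way would be carried forward into that design.

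**Working it through.** The plan derives no figure on this point, so there is none to reproduce. The check is a count of Table 1 followed by simple arithmetic.

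**Inputs**

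- Baseline length B: non-repeating whole weeks from 2 to 7 (section 3.6). Six children (section 3.5) therefore use 2, 3, 4, 5, 6 and 7 once each: sum 27, mean 27/6 = 4.5.
- Seat period: 8 weeks (section 3.1).
- Transition visits c1 and c2: duration not given, left out.

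**Step 1: ratings before the seat.** Read against the 23 time-point columns of Table 1, COPM has 1 (b1). PQRS has 3 × B marks, from 3 × 2 = 6 to 3 × 7 = 21 per child. One value gives no estimate of level variability, trend or autocorrelation within baseline. The extra ratings at t1 and t2 in section 3.17 fall within seat use and cannot serve as pre-seat values.

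**Step 2: share of the interval before the seat.** From b1 to the end of seat use is B + 8 weeks, that is 10 to 15. The share in the usual seat is B/(B + 8):

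| B (weeks) | 2 | 3 | 4 | 5 | 6 | 7 |
|---|---|---|---|---|---|---|
| B/(B + 8) | 20% | 27% | 33% | 38% | 43% | 47% |

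Pooled over six children: 27/(27 + 48) = 27/75 = 36%.

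**Step 3: what a drift would do.** The documents give no COPM drift. Assume a linear drift of d points per week, unrelated to the seat. The baseline part is d × B, with mean 4.5d. If the drift continues, the seat period adds 8d.

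| Assumed d | Baseline part, by child | Baseline part, mean | Seat-period part | Total, mean |
|---|---|---|---|---|
| 0.05 | 0.10 to 0.35 | 0.225 | 0.40 | 0.625 |
| 0.10 | 0.20 to 0.70 | 0.45 | 0.80 | 1.25 |
| 0.20 | 0.40 to 1.40 | 0.90 | 1.60 | 2.50 |

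A negative d gives the same sizes with the opposite sign and would hide a seat effect.

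**Step 4: what an end-of-baseline reference removes.** It removes the baseline part only. At d = 0.10 that is 0.45 of 1.25 points, and 0.80 remains.

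**Step 5: effect on the planned interval, as an illustration.** In 20,000 simulated series of six children there was no seat effect, an assumed error SD of 1 point per rating and a drift of 0.1 per week that stops when the seat arrives. With b1 as reference, the 95% interval for mean change lay wholly above zero in 9.1% of runs. With the last baseline rating as reference it did so in 2.4%. That recovery depends on the drift ending before the seat.

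**The case against.** **The conflict may be one of wording.** Section 3.17 ties repeated collection during intervention to PQRS, sensors and accelerometers, and its later data-point sentences name only PQRS and sensor data. Section 3.19 speaks of baseline, post-intervention and follow-up, which fits Table 1. On this view b1–b7 merely names the phase. Read literally, though, section 3.17 has COPM rated through baseline, and the gap then disappears. So the gap holds under Table 1, which is the specific schedule. Whichever reading is meant, the text has to be settled.

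**COPM may be a pre/post measure by choice.** The single-case analysis in section 3.19.1 is built around PQRS, which scores the same goals, is rated blind and has ample baseline data. It would give indirect evidence of change before the seat. Parents asked for little written feedback (section 1.1). This stands as a reason to keep any addition small. It does not supply a COPM reference, because PQRS is a different scale with a different rater.

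**Several stronger readings are tempting but not supported.**

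- A reader might infer that the COPM change is biased in favour of the seat. No passage gives a drift, or its sign.
- A reader might take it as stated that goals are chosen and first rated in one interview. Section 3.12 says one assessment does both jobs, and b1 is the only COPM before the seat, so the inference is reasonable. It is not stated, and the baseline flow chart (Figure 2a) is not available here.
- A reader might expect a later reference to remove the goal-visit effect. Section 3.15 makes its concession in describing the seat intervention, so the visits, and any effect of them, may continue through it.
- A reader might extend the point to RAACS and PedsQL, which are also rated once before the seat. They are secondary, and nothing says they select goals.

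**The varying baseline length might be used between children.** Regressing COPM change on B is not planned. With six children and one prior rating it could not separate a goal-setting step common to all from the seat effect.

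**Conclusion.** The point holds for the schedule in Table 1. COPM has a single pre-seat rating, so the randomised baseline gives it no within-child control. COPM change during 20% to 47% of the interval (36% pooled) enters the change read as the intervention's impact. Sections 3.14 and 3.17 disagree with the table and must be reconciled with it.

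The shares follow from the documents, leaving out the transition visits. The point sizes in COPM units rest on assumed drifts, and the simulated percentages also rest on an assumed error SD. They illustrate a range and do not estimate a bias.

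This is a cheap and worthwhile improvement, not a fatal defect. The study is a six-child feasibility series without a power calculation, no decision threshold rests on COPM, and section 3.9 says it will explore how the measure works in this setting. It should still be settled before recruitment, which section 4 says has not begun, because baseline ratings that are not taken cannot be recovered later.

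**What to change.** 1. In Table 1, add a COPM re-rating of the goals already chosen, by the same respondent, at the child's last baseline visit (b2 to b7 according to allocation).
2. Use that rating as the reference for COPM change. Report the change from b1 to the last baseline visit beside it, as the change seen in the usual seat.
3. Bring sections 3.14 and 3.17 into line with Table 1, including the ratings at t1 and t2.
4. State that effects of visits or of time that continue during seat use are not removed.

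The cost is one short interview per child at a visit that already takes place, plus the text and table edits. Limiting the addition to COPM keeps the burden on parents small. Two baseline ratings give a usual-seat change for each child, but still too little to characterise trend or autocorrelation.

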**ANALYSIS AND REPORTING**																							
Study Forms																							X
Study Files																							X
Study Findings																							X
Summary Letter																							X

Abbreviations: e: Enrolment, b: baseline, c: configuration of seat, t: treatment, p: post-intervention, f: follow up, co: close out, GMFCS: Gross Motor Function Classification System, MACS: Manual Ability Classification System, BFMDRS: Burke–Fahn–Marsden Dystonia Rating Scale, PQRS: Performance Quality Rating Scale, COPM: Canadian Occupational Performance Measure, RAACS: The Responsive Augmentative and Alternative Communication Style Scale, QoL: Quality of Life, and PedsQL: Paediatric Quality of Life. Note: X: indicates when assessment will take place. The intervention (dynamic seating provision) is represented with blocked colour across t1–t8.

**Table 2 healthcare-08-00011-t002:** A table of sensor data to be collected and the initial analyses to be applied.

Sensor	Measurement, Example Data Points	Analysis	Output Parameters
Seat occupancy	Time of seat entry Time of seat exit Date Time Data 2017-08-21; 12:33:45;1 2017-08-21; 12:33:45;0	Continuous seat occupancy profile: Identification of initiation time, duration and exit time of each seat occupancy event.	Weekly seat occupancy ratio (occupied time / unoccupied time)—for what proportion of the day is the seat used on average? Mean seat occupied session duration per week—how long is each session? Mean daily seat occupancy profile per week—when is the seat used? Seat entry frequency per week—How often is the seat used?
3 axis integrated accelerometer	Night Accelerations of the wrist and ankle ($a_{W}$ and $a_{A}$) Date Time x y z 2017-08-21; 12:33:45.67;123;456;243	Night Acceleration vector magnitude: $\left|a\right|=\sqrt{a_{x}^{2}+a_{y}^{2}+a_{z}^{2}}$ Times when acceleration vector magnitude is above and below sleep/awake threshold.	Night Sleep quality index—proportion of time in motion above threshold intensity—How well does the child sleep? Sleep time—total time per night not in motion above threshold intensity—For how much time is the child asleep each night?
	Day Accelerations of spine (vertebra T1) and left and right thighs during seat use: ($a_{S},\;a_{TL}\;and\;a_{TR}$)	Day Intensity of motion: time averaged amplitude of xyz acceleration vector time averaged amplitude of jerk (rate of change of acceleration)	Day Motion profile—How active is the child throughout the day? Maximum and minimum motion intensities—What are the maximum and minimum activity levels? When do they occur?
9 degree of freedom motion and orientation sensor	Movement of the child’s wrist during a reaching task. Measurement of the acceleration, rotation and geomagnetic field orientation of the child’s wrist. 3 axis acceleration (accelerometers) 3 axis rotation (gyroscopes) 3 axis geomagnetic field orientation (magnetometers)	Motion path of the child’s wrist derived from acceleration and orientation data	Output parameters are to be determined from analysis of the data in the context of the video and PQRS assessment. Parameters sought are to be representative of the ‘smoothness’ and efficiency of the child’s hand motion.

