### 3.18. Sensor-Based Measurements

**Seat occupancy profile:** This will be measured continuously at baseline, during and after the intervention periods, using a simple pressure switch and data logger attached to the participant’s seat. The data logger will record when and for how long the seat is occupied. The system requires no intervention from the participant or their family between setup and removal.

**Sleep quality:** This will be measured using a simple lightweight inertial measurement unit (IMU) attached to the child using a wrist or ankle band. This measurement has been trialed with children during the previous and preparatory KiTE 1 project [23]. Parents will be asked to ensure that their children wear the sensor band for at least 2 nights per week during the baseline and intervention periods. The sensors require no intervention by the parent other than placing the sensor on the child’s wrist or ankle and switching it on when they go to bed.

**Daytime activity intensity and frequency:** To be measured using the IMUs for 2 days per week, preferably two days either side of a measured night. The sensors will be used to measure how much the child moves, and the intensity and duration of their movement.

Sensor data collection and analysis is shown on Table 2. It will be collected by a study researcher during weekly visits to the participant and transferred to secure encrypted storage using the project laptop. Data will be coded and pseudonymised on collection.

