### 3.19. Data Analyses Plan

A full statistical analysis plan for the study will be available. Descriptive statistics will be used to summarise demographic characteristics of the participants, including age and diagnosis. Functional ability will be classified using GFMCS and MACS/Mini-MACS.

Primary and secondary outcome measures across the domains of the ICF will be completed at baseline, post-intervention and follow up. There will be two types of data depending on whether the within- or between-subjects data are examined. Within subject data will evaluate the SCED data with direct replications. Between-subjects evaluation for outcome measures pre-intervention, post-intervention and follow up will be used for all measures calculating means and 95% confidence intervals for overall change. There is no planned interim analysis.

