#### 3.19.1. Data from SCED

To describe the impact of the intervention in the single-case experimental studies, pre-intervention and post-intervention raw scores will be examined in all outcome measures. Analysis of PQRS changes will be evaluated using an appropriate analysis for SCED. The analysis will be guided by interpretation of the visual representation of the results; whether there is auto-correlation on baseline data; and whether there is baseline trend present in the data set. We will follow the recommendations from the Single-Case Reporting Guideline in Behavioural Interventions (SCRIBE) [24]. Visual analysis will be undertaken to evaluate changes in the domains of means, levels, trends, variability, latency and consistency. This will be followed by statistical analysis of the graph which will vary depending on serial dependency. Estimated effect size will be calculated using a suitable regression approach for SCED. We will initially fit a naïve linear regression model using ordinary least squares for reference only. We will use the Tau-*U* approach as it takes into account baseline trend and is considered one of the most robust effect size methods in SCED [25].

SCED uses repeated measures and therefore provides multiple data points. The extended baseline and intervention phases will result in many data points. PQRS can be applied multiple times within the same practiced task, given it is scoring the quality of performance rather than one-off task performance [20]. Therefore, each task step within a task is assigned a data point.

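### The weekly seat occupancy ratio in Table 2 is defined as an odds but described as a proportion of the day, so read as described it overstates use and change in use

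*Protocol article*

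**What the plan says.** Section 3.10 of the protocol article states "There will be three primary outcome measures". The third is seating tolerance: "seating tolerance will be objectively measured using sensors attached to the chair that will capture the duration and frequency of its use". Section 3.18 describes the source data: "The data logger will record when and for how long the seat is occupied".

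Table 2 lists four outputs from this sensor. The first is "Weekly seat occupancy ratio (occupied time / unoccupied time)—for what proportion of the day is the seat used on average". The others are mean session length ("Mean seat occupied session duration per week—how long is each session"), the daily profile of use, and the number of seat entries per week. Section 3.19.2 refers to Table 2 for the derived parameters and gives no other formula.

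Section 3.19 says that between-subjects evaluation before the intervention, after it and at follow-up "will be used for all measures calculating means and 95% confidence intervals for overall change". Section 3.9 names, as a feasibility aim, the standard deviation of the primary outcome needed to size a later trial.

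**The concern.** The formula and its description, on the same line of Table 2, are two different quantities. Time occupied divided by time unoccupied is an odds: it has no upper limit and passes 1 once the seat is used for more than half of the time counted. A proportion of the day divides by all the time counted and cannot exceed 1. Elsewhere in Table 2 a proportion is described as such: "Sleep quality index—proportion of time in motion above threshold intensity". No other part of the article corrects the occupancy formula.

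If the number is computed as written and read as described, use of the seat looks greater than it was, and so does any change. The stretch grows with the level of use, so equal gains in hours do not count equally across children. With six children, a mean change then leans towards those who sit longest. A standard deviation on this scale would take the same distortion into the planning of the next trial.

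**Working it through.** **Inputs.** The formula and its description come from Table 2, and the planned summaries from sections 3.9, 3.19 and 3.19.1. The article gives no value for this parameter, so there is no figure to reproduce. It also gives no hours of use, and does not say whether unoccupied time covers 24 h or the waking day. The hours below, and day lengths of 24 h and 12 h, are assumptions.

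**Level.** Let O be time occupied, U time unoccupied and p = O/(O + U). The formula gives r = O/U = p/(1-p). Hence r/p = 1/(1-p), which is above 1 for every p between 0 and 1.

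| Use per day | 24 h day: p | 24 h day: r | Excess | 12 h day: p | 12 h day: r | Excess |
|---|---|---|---|---|---|---|
| 1 h | 0.042 | 0.043 | 4% | 0.083 | 0.091 | 9% |
| 2 h | 0.083 | 0.091 | 9% | 0.167 | 0.200 | 20% |
| 4 h | 0.167 | 0.200 | 20% | 0.333 | 0.500 | 50% |
| 6 h | 0.250 | 0.333 | 33% | 0.500 | 1.000 | 100% |
| 8 h | 0.333 | 0.500 | 50% | 0.667 | 2.000 | 200% |

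For example, 4 h in a 24 h day gives 4/20 = 0.200 by the formula, against 4/24 = 0.167.

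**Change.** r2 - r1 = (p2 - p1)/[(1-p1)(1-p2)], so a change in the proportion is multiplied by 1/[(1-p1)(1-p2)].

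| Change in daily use | 24 h: change in p | 24 h: change in r | Factor | 12 h: change in p | 12 h: change in r | Factor |
|---|---|---|---|---|---|---|
| 1 to 2 h | 0.042 | 0.047 | 1.14 | 0.083 | 0.109 | 1.31 |
| 2 to 4 h | 0.083 | 0.109 | 1.31 | 0.167 | 0.300 | 1.80 |
| 4 to 6 h | 0.083 | 0.133 | 1.60 | 0.167 | 0.500 | 3.00 |
| 6 to 8 h | 0.083 | 0.167 | 2.00 | 0.167 | 1.000 | 6.00 |

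**Weight between children.** On the 24 h base, one child going from 2 to 4 h and another from 6 to 8 h both gain 0.083 of the day. By the formula they gain 0.109 and 0.167, so the second counts 0.167/0.109 = 1.53 times as much in a mean.

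**Averaging over the week.** Take daily use of 2, 2, 4, 4, 6, 8 and 9 h in a 12 h day, a total of 35 h out of 84 h. The proportion is 35/84 = 0.417, whether taken from the weekly totals or as the mean of the seven daily proportions. The odds from weekly totals is 35/(84 - 35) = 0.714, but the mean of the seven daily odds is 1.057. The odds therefore also depends on how the average is formed.

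**Ranks.** The derivative of r with respect to p is 1/(1-p)², which is positive. Over a common denominator, r and p put weekly values in the same order when both come from weekly totals. Indices built on pairwise order do not change.

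**The case against.** The strongest reply is that the ratio is not the primary endpoint. Section 3.10 describes seating tolerance by how long and how often the chair is used. Mean session length and entry frequency in Table 2 match that most directly, and neither uses this formula. Section 3.19.2 presents the Table 2 parameters as proposals, and the table's own title calls the analyses initial. This stands. A reader might infer that a primary endpoint is computed wrongly, but the article supports less: one of four parameters listed for a primary outcome is misdefined, and none is named as the deciding one.

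A second reply is that little is lost. The log keeps every entry and exit, and a single ratio converts back by p = r/(1 + r). For the single-case analysis the article says "We will use the Tau-*U* approach as it takes into account baseline trend", and a rank-based index on weekly values is unaffected. This also stands, within limits. A mean, confidence interval or standard deviation calculated on the odds scale cannot be converted back in that way, and those are the summaries that sections 3.9 and 3.19 call for.

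A third reply is that the error may be small. At 1 to 2 h on a 24 h base it is about 4% to 9% in level. That is correct, and no part of the article supports assuming long hours of use. The direction, however, is always overstatement.

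A reader might also infer that weekly summaries leave a child with a 2-week baseline only two values, below a protocol minimum of three. The article does not support this. The minimum of three under Outcome Evaluation concerns video-recorded goals, the figure in section 3.5 is a general recommendation, the logger runs continuously, and nothing limits the analysis of occupancy to one value per week.

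The full analysis plan, which is not shown, may put the formula right. The point remains because the article states a formula that contradicts its own description, which is different from leaving a detail out.

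**Conclusion.** The point holds as a definitional error in one Table 2 parameter. The formula is an odds and its description is a proportion. Read as described, the level is overstated by 1/(1-p) and a change by 1/[(1-p1)(1-p2)]. The direction is certain from the algebra. The size is not, because it rests on assumed hours and day length: about 4% at 1 h to 50% at 8 h in level on a 24 h day, and 9% to 200% over the same hours on a 12 h day.

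The error reaches means and 95% confidence intervals for change, any regression effect size fitted to this parameter, and any standard deviation of it used to size the later trial. It does not reach Tau-U on weekly values or the other three occupancy parameters. It does not show that the seating-tolerance outcome as a whole is invalid.

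**What to change.** In Table 2, define the parameter as occupied time divided by the sum of occupied and unoccupied time, counting only validly logged time, and state whether the denominator is the full 24 h or the waking day. Mean hours of use per day would serve equally well. If the ratio is kept for some purpose, drop its description as a proportion and do not carry its mean or standard deviation forward as one.

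The cost is one line of text and one line of code. The entry and exit times already logged are enough, and no further sensor or visit is needed. Section 4 says that recruitment has not started, so the change can be made before any data exist.
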